## Methods and analysis

### Study design

COG-UK HOCI is a prospective, interventional, superiority clinical study, comprising three distinct phases with a possible fourth, dependant on interim data analysis.

In the first phase, all sites will collect baseline (non-interventional) eligible patient data for a period of 4 weeks to characterise each site’s usual practice in infection control in response to hospital-onset COVID-19 cases. This phase may include standard of care use of genome sequencing (eg, limited outbreak response analysis).

In the second and third phases, the study intervention will be applied on top of standard of care infection control practices.

The second phase requires ‘rapid’ turnaround of genome sequencing and sequence linkage report generation (ie, within 48 hours of first diagnostic SARS-CoV-2 PCR-positive result). This phase will be applied to all hospital onset COVID-19 cases meeting the eligibility criteria over an 8-week period.

The third phase is similar to the second, except that a 5–10 day turnaround time of genome sequencing and sequence report generation should be applied to mimic the use of a central sequencing laboratory. This phase will apply to all sites and last for 4 weeks.

The second and third phases may be applied in the reverse order at some sites, both for logistical reasons (ie, fine-tuning of rapid turnaround of whole-genome sequences) and also to ensure differences between sites in the calendar dates of each phase.

On review of interim analysis data, the study’s joint oversight committee may recommend a fourth phase for all sites comprising a second baseline period; this would be applied where the initial baseline data collection period occurred at a time of very high or low COVID-19 prevalence at the sites, whereby collecting data on standard practice could be unviable.

This will be a sequential study, with each National Health Service (NHS) Trust acting as its own control.

The total study duration per site will accordingly be 16–20 weeks, though it is likely that pauses in data collection will occur over the winter holiday break period due to most sequencing labs closing or moving to skeletal operations during this time.

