### Sample size and power

The projected total sample size is 2380 patients.

There is uncertainty in the number of HOCIs that will be identified at each site during each of the intervention periods, with the rapid testing phase being 8 weeks’ duration. Based on clinical experience of first wave and discussion with the principal investigators, we assume there may be an average of 10 HOCIs/week per site during this intervention period, a total of 80 per site. Within a typical site this will allow us to estimate the proportion of HOCIs with genotypic linkage to any other case(s) not detected by IPC processes with minimum precision of±9.4%. Similarly, we can estimate the proportion of HOCIs where an action is taken that would not have occurred without sequencing within±9.4%. We shall also calculate pooled estimates of these proportions across the 14 sites, leading to estimation within±6.5% assuming an intracluster correlation coefficient of 0.05.

Comparing the proportion of HOCIs with genotypic linkage to any other case(s) not detected by IPC processes between rapid testing and slow testing phases across all sites, the study would have at least 80% power to detect a percentage point difference of 11%. This corresponds to a two-sided test with alpha=0.05, considering proportions of 55.5% vs 44.5% which would be associated with minimum power for a difference of this magnitude.

For the outcome of weekly incidence of IPC-defined HOCIs, using an approximate normal distribution for weekly counts there is 86.7% power to demonstrate a reduction from 12 IPC-defined HOCIs per week in the baseline phase to 10 per week during the rapid testing phase across all sites, under 5% significance level two-tailed testing. However, these calculations correspond to a variance of 12 for weekly counts based on the Poisson distribution, but the presence of over-dispersion of weekly counts would lead to a lower power to detect a difference. Using an overdispersion parameter of 0.82 based on retrospective analysis of data from Sheffield and Glasgow (dataset as described by Stirrup *et al*) results in 81% power to detect a reduction in mean weekly incidence from 12.5 to 10.^10^

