### Statistical analysis

Summary statistics will be presented for each study phase (baseline, rapid local lab and central lab interventions) and each site, which will be percentages for binary outcomes such as whether transmission linkage for each HOCI was previously undetected. The frequency of IPC-defined HAIs, IPC-defined outbreak events and IPC with sequencing-defined outbreak events will be expressed as rate per week per 100 inpatients.

The outcomes of genotypic identification of transmission linkage not suspected at initial IPC investigation and impact of sequencing on IPC actions are only defined for the intervention periods. For such outcomes, the focus of analysis is to calculate summary statistics overall and for each site, which can be informally compared with the degree to which it is thought each site was able to fully implement the intervention. Variation over time within each site will also be explored, and the proportions will be compared between the rapid sequencing and delayed sequencing intervention periods.

The main analyses for the primary and secondary outcomes will be carried out on an intention-to-treat basis according to the defined study phases. However, sensitivity analyses will be conducted excluding study sites and/or periods with suboptimal implementation of the study intervention, both in terms of overall population sequencing coverage for HOCIs and the turnaround time for sequence reports being returned to IPC teams.

For outcomes defined in both the baseline and intervention periods, such as incidence of IPC-defined HAIs and the number IPC-defined hospital outbreaks, this can be informally compared between the baseline, intervention and (where implementation is justified) final control periods within sites. A formal analysis will be conducted based on negative binomial regression to detect the change in the incidence rate of each event type between baseline, intervention and control phases within site, including the current proportion of inpatients who are SARS-CoV-2 positive as a fixed effect and exposure ‘determined’ by the number of SARS-CoV-2-negative inpatients in that week. These analyses will also include adjustment for the proportion of HCWs at each site who have received at least one vaccine dose and a smoothed adjustment for calendar time. This will lead to an adjusted incidence rate ratio for the intervention effect, presented with a 95% CI.

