### Study timelines

Sites will be opened using a staggered approach from October 2020 to January 2021 in order to provide the greatest likelihood of each phase of site activity covering peaks, troughs and moderate incidences of community prevalence and, therefore, likely hospital admissions of patients with COVID-19.

Patient recruitment at sites will run for 6 months from late October 2020 to end April 2021.

See table 1 for study schedule.

**Table 1 T1:** Study schedule

Timepoint (site dependent)	6 months	4 weeks	8 weeks	4 weeks	4 weeks	6 months
Study stage (site dependent)	Set up	First baseline/ control (daily)	Intervention sequencing result <48 hours (daily)*	Intervention sequencing result >4 days (daily)*	Second baseline/ control (where justified, daily)	Data cleaning, analysis and reporting
Site identification	X					
Site team discussion on sampling ability, staffing availability and logistics	X					
Initiation of contracts, R&D approvals	X					
NHS samples begin to be processed locally under COG-UK approvals (not study-related)	X					
NHS samples to be processed under COG-UK approvals, either locally or at Sanger		X	X	X	X	
Intervention reports generated			X	X		
Intervention reports returned to site ICTs (<48 hour)			X			
Intervention reports returned to site ICTs (>4 days)				X		
ICTs evaluate reports, seeking Expert Sequence Interpretation Team views if needed			X	X		
Case reports for HOCIs		X	X	X	X	
Process evaluation—qualitative interviews /analysis			X	X	X	x
Process evaluation—programme theory development and refinement	x		x	x	x	x
Interim analysis and views from TSC-DMC whether second baseline/control state acceptable					X†	
Data cleaning		X	X	X	X	X
Final data lock and analysis						X
Reporting/publication						X

*The order of ‘rapid’ phase (<48 hour turnaround time) and ‘slow’ phase may be swapped prior to commencement of either on agreement with the Sponsor. The option is offered to facilitate logistics/set-up at sites.

†TSC-DMC review should take place to determine whether it would be considered ethical to request sites have a second period of baseline/control (where sequencing data is not provided to IPC teams). This would only be on the basis that it is unclear from the initial baseline and intervention comparison whether there is a significant benefit; in cases where it is clear there is either benefit to the intervention or no benefit, then the second baseline would not take place.

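### The 86.7% and 81% power for the incidence outcome belong to an unadjusted two-group comparison, not to the planned within-site model with a calendar-time smooth, which has less power in the three-phase design

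*Protocol article*

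**What the plan says.** In the protocol article, Sample size and power, the incidence calculation reads "using an approximate normal distribution for weekly counts there is 86.7% power to demonstrate a reduction". The assumed fall is from 12 cases weekly at baseline to 10 in the rapid phase, tested two-sided at the 5% level. The variance of a weekly count is taken as 12. The section then warns that overdispersion lowers power, introduces an overdispersion parameter of 0.82, and says that this "results in 81% power to detect a reduction in mean weekly incidence from 12.5 to 10". Overdispersion is its only caution. Neither site nor calendar time is mentioned.

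Statistical analysis sets out the formal test. It is a negative binomial regression "to detect the change in the incidence rate of each event type between baseline, intervention and control phases within site", adjusted for current inpatient positivity, staff vaccination and "a smoothed adjustment for calendar time". The adjusted incidence rate ratio with its 95% CI is the reported effect. Unadjusted phase contrasts are to be compared only informally.

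Study design gives 4 baseline weeks, 8 rapid weeks and 4 slow weeks per site, always with baseline first. Some sites may swap rapid and slow. A further 4-week baseline is conditional. "This will be a sequential study, with each National Health Service (NHS) Trust acting as its own control". Study timelines adds: "Sites will be opened using a staggered approach from October 2020 to January 2021".

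**The concern.** The printed power describes a test that is not the formal analysis. Adjusting for covariates often preserves or raises power, so powering on a simpler test is usually harmless. That cannot be assumed here. Every site moves from baseline to intervention, and the permitted swap concerns only the two intervention phases. Within a site, phase is therefore largely confounded with calendar time. When the model contains both a site effect and a time smooth, much of the before-after contrast is absorbed by the smooth.

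This outcome is the trial's test of whether sequencing reduces hospital-acquired infection. A null adjusted rate ratio read against a stated 81–87% would look like fair evidence of no effect, when the test may have had much less chance of detecting the assumed reduction of 17% (12 to 10) or 20% (12.5 to 10). The oversight committee's decision on a second baseline turns partly on whether benefit is still unclear, so it too needs the power of the adjusted comparison.

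**Working it through.** **Inputs from the protocol article.** 14 sites (Setting); 4, 8 and 4 weeks for baseline, rapid and slow (Study design); rates, variance 12, parameter 0.82 and two-sided 5% level (Sample size and power).

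**Assumptions, because the documents are silent.** Openings spread over 8–13 weeks; 0, 4 or 7 sites with swapped order; spline with 3–6 degrees of freedom; variance = 1.82 × mean for the overdispersed case. This last reading is inferred because it reproduces the 81%. Reading 0.82 as a negative binomial dispersion (variance = mean + 0.82 × mean²) gives only about 20% from the crude formula.

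**1. Reproducing the printed figures.** Power = Φ(difference / SE − 1.96), with SE = √[variance × (1/n₁ + 1/n₂)] and n₁ = n₂ = 14 × 4 = 56 site-weeks.
- 12 to 10: SE = √(12 × 2/56) = 0.655; 2/0.655 = 3.055; Φ(1.095) = 86.3% (stated 86.7%).
- 12.5 to 10: variance 12 × 1.82 = 21.84; SE = √(21.84 × 2/56) = 0.883; 2.5/0.883 = 2.831; Φ(0.871) = 80.8% (stated 81%).

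The formula has no site or time term. With all eight rapid weeks (56 v 112 site-weeks) it gives 94.2% and 90.5%.

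**2. Log-linear model with site effects and no time term, 4 v 8 weeks.** Power = Φ(|log IRR| / SE − 1.96).
- Poisson: SE = √[1/(56 × 12) + 1/(112 × 10)] = 0.0488; log 1.2 = 0.182; ratio 3.74; power 96%.
- Overdispersed: SE = √{1.82 × [1/(56 × 12.5) + 1/(112 × 10)]} = 0.0650; log 1.25 = 0.223; ratio 3.43; power 93%.

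Site effects alone therefore cause no loss.

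**3. Adding calendar time.** SE is taken from the inverse information matrix of a log-linear count model with rapid and slow indicators, a site effect and a natural cubic spline of calendar week.

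| Model | 12 to 10, Poisson | 12.5 to 10, 1.82 × mean |
|---|---|---|
| Site fixed effects, spline 3–6 df | 53–67% | 46–59% |
| Site fixed effects, straight-line time only | 57–71% | 50–63% |
| Random intercept, SD 0.5 (12-week spread, 4 df) | 58–67% | 52–60% |
| Random intercept, SD 0.1 (same) | 77% | 72–73% |
| Random intercept, SD 0.05 (same) | 82–83% | 76–78% |
| No site differences | 71–88% | 63–82% |
| Site fixed effects, spline, second baseline at all sites | 91–98% | 86–96% |

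SDs are between sites on the log scale. All rows except the last exclude the second baseline.

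For the first row, the SE can be recovered from the power. At 53%, 0.182/(1.96 + 0.075) = 0.090; at 67%, 0.182/(1.96 + 0.440) = 0.076. Against 0.0488, the SE grows by a factor of about 1.6 to 1.8.

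These are large-sample approximations. They leave out serial correlation and the inpatient-positivity covariate.

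**The case against.** The strongest reply is that nothing is miscalculated. The section names its method, the figures reproduce, and it never says that they apply to the adjusted rate ratio. That stands: a reader might infer an arithmetic error, and there is none. The fault is that the stated power and the stated analysis do not match, and that the only caution given is overdispersion.

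A reader might also infer that true power is a fixed figure near one half. The documents do not support that. Opening dates, number of swaps, smoothness and form of site effect are not given, and comparison within site does not oblige fixed effects. With nearly identical sites modelled as random, power comes close to the printed values. A heavily penalised smooth does not rescue the fixed-effects version, however, since even a straight line in time leaves 57–71% and 50–63%.

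The second baseline is a real part of the design and restores power. But it is conditional, the sample-size section does not rely on it, and the 86–98% assumes that every site completes it. A site opening on 1 January 2021 would finish 16 weeks on 23 April and 20 weeks on 21 May, after the stated end-April close of recruitment.

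Two further inferences go too far. One is that the effect is identified only from staggered openings and swaps. That would be true of free week effects, but against a smooth curve the step at a phase change also carries information: with simultaneous openings, no swaps and a 3–4 df spline, Poisson power was still 34–37%. The other is that vaccination adjustment would cut power materially further. With an assumed uptake curve it changed the result by about 2 points or less. Adjusting for inpatient positivity could even reduce residual dispersion, if 0.82 was estimated without it; the article does not say.

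Finally, the printed figures match four rapid weeks per site rather than eight, which might look like a built-in reserve. It is not enough: the eight-week design starts at 96% and 93% before the time term and still falls to the ranges shown.

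**Conclusion.** The concern holds as a mismatch between the power calculation and the planned analysis. The 86.7% and 81% apply to an unadjusted comparison of weekly counts. In the three-phase design, adjusting for both site and calendar time lowers power below those figures in every version tried that allowed sites to differ. The size is conditional on the assumptions listed: about 53–67% and 46–59% with site fixed effects and a 3–6 df spline, rising to about 77% and 73% with random intercepts at SD 0.1, and reaching the printed figures only as site differences vanish. With the second baseline at all sites, the planned analysis has at least the printed power. The direction is firm; no single replacement figure follows from the documents.

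**What to change.** In Sample size and power, state that 86.7% and 81% are for an unadjusted before-after comparison. Replace or supplement them with power and the detectable rate ratio under the model in Statistical analysis (site effect, baseline/rapid/slow terms, calendar smooth), using the planned or actual opening dates and phase order. Give the results with and without the second baseline, and state the form of the site effect, the smoothness and the meaning of the 0.82. Simulation under the planned model would be suitable. Do not insert a fixed figure such as 50–65% as though the documents determined it.

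The cost is one recalculation and a wording change, with no extra patients, sites or data. The stated power for the three-phase design will probably be less favourable.

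### The printed powers of 86.7% and 81% for the incidence primary outcome do not follow from 14 sites with 4 baseline and 8 rapid weeks, and they are given for different effect sizes

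*Protocol article*

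**What the plan says.** Under Sample size and power, the protocol article treats the weekly incidence outcome by a normal approximation ("using an approximate normal distribution for weekly counts") and tests "under 5% significance level two-tailed testing". It states that "there is 86.7% power to demonstrate a reduction from 12 IPC-defined HOCIs per week in the baseline phase to 10 per week" in the rapid phase, and explains that "these calculations correspond to a variance of 12 for weekly counts based on the Poisson distribution". It warns that overdispersion would lower the power, and continues: "Using an overdispersion parameter of 0.82 based on retrospective analysis of data from Sheffield and Glasgow" "results in 81% power to detect a reduction in mean weekly incidence from 12.5 to 10".

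The section does not give the number of site-weeks used in each phase, or the variance function in which 0.82 is a parameter. The design itself is stated. Study design sets 4 baseline weeks and 8 rapid weeks, and Setting gives 14 sites. Under Statistical analysis, the planned model is negative binomial: "A formal analysis will be conducted based on negative binomial regression to detect the change in the incidence rate".

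**The concern.** Every input needed to recompute the 86.7% is printed, and the recomputed value differs by more than 7 percentage points. The 81% cannot be recovered from the same design either. In addition, the two sentences use different effects, a fall of 2 per week and then a fall of 2.5. The step from 86.7% to 81% therefore does not show what overdispersion costs.

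This is one of two primary outcomes. How a null result on incidence is read depends on how much power the design had for a plausible reduction. As printed, a reader cannot tell which comparison the powers describe, or whether the design keeps 80% power for 12 to 10 once overdispersion is allowed for.

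**Working it through.** **Inputs (all from the protocol article)**
- Two-sided 5% test, so the critical value is 1.96 (Sample size and power).
- 14 sites (Setting; Sample size and power).
- 4 baseline weeks and 8 rapid weeks (Study design), giving 14 × 4 = 56 and 14 × 8 = 112 site-weeks.
- Poisson case: 12 to 10 per week, variance 12.
- Overdispersed case: 12.5 to 10 per week, parameter 0.82.

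**Check that the counts are per site and the design is as read.** The same section assumes 10 cases per week per site in the rapid phase. With 12.5 at baseline and 10 in both sequencing phases, 14 × (4 × 12.5 + 8 × 10 + 4 × 10) = 14 × 170 = 2380. This is exactly the projected sample size.

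**Formula.** Power = Φ(d / SE − 1.96), with SE = √(v₁/n₁ + v₂/n₂).

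**1. Poisson case, stated design (printed: 86.7%)**
- Variance 12 in both phases: SE = √(12/56 + 12/112) = 0.567; 2/0.567 = 3.53; power 94.2%.
- Variance 12 and 10: SE = √(12/56 + 10/112) = 0.551; power 95.3%.
- Log-rate, square-root and t-test variants on site-weeks give 93.9 to 96.2%. Site-level t-tests on the 14 sites give 90.3 to 93.7%. None comes within 2 points of 86.7%.

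**2. Overdispersed case, 12.5 to 10, stated design, variance = 1.82 × mean (printed: 81%)**
- Common variance 12.5 × 1.82 = 22.75: SE = √(22.75/56 + 22.75/112) = 0.781; 2.5/0.781 = 3.20; power 89.3%.
- Variances 22.75 and 10 × 1.82 = 18.2: SE = 0.754; power 91.2%.
- The log scale gives 93.0%. The lowest site-level paired t-test gives 84.1%. None comes within 2 points of 81%.

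**3. Which design does come close to the printed pair?**

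| Comparison | 12 to 10, Poisson | 12.5 to 10, overdispersed (1.82 × mean) |
|---|---|---|
| Printed | 86.7% | 81% |
| 56 v 112 site-weeks (stated design) | 94.2 to 95.3% | 89.3 to 91.2% |
| 56 v 56 site-weeks (14 sites, 4 v 4 weeks) | 86.3% (variance 12) | 80.8% (variance 12 × 1.82); 79.2% (variance 12.5 × 1.82) |
| 40 v 80 site-weeks (10 sites, 4 v 8 weeks) | 86.6% (variances 12, 10) | 80.0% (variances 22.75, 18.2) |

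Both printed figures are approached with one variance function, but only for a smaller comparison than the one described.

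**4. Same effect in both cases, stated design.** Take 12 to 10 with variance = 1.82 × mean.
- Common variance 12 × 1.82 = 21.84: SE = √(21.84/56 + 21.84/112) = 0.765; 2/0.765 = 2.61; power 74.4%.
- Variances 21.84 and 18.2: SE = 0.743; power 76.8%.

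Like for like, overdispersion takes power from 94–95% to 74–77%.

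**5. Sensitivity case only: 0.82 as the mean-dispersion alpha**, variance = mean + 0.82 × mean².
- Baseline: 12.5 + 0.82 × 156.25 = 140.6. Rapid: 10 + 0.82 × 100 = 92.
- Difference scale: SE = √(140.6/56 + 92/112) = 1.826; 2.5/1.826 = 1.37; power 27.7%.
- Log rate ratio: SE = √((1/12.5 + 0.82)/56 + (1/10 + 0.82)/112) = 0.156; ln(1.25)/0.156 = 1.43; power 29.9%. Simulated negative binomial fits (600 runs) gave 30.7%.
- For 81% at 56 v 112 site-weeks, alpha would have to be about 0.14.

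**The case against.** The strongest reply is that the mismatch is on the safe side. If 0.82 means variance = 1.82 × mean, the stated design has more power than printed for both printed effects, so nobody is led into overconfidence about those two comparisons. That stands, and it limits the weight of the point. It does not make the printed figures correct for the printed design. It also does not cover the 12 to 10 effect with overdispersion, where power falls below 80%.

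A reader might infer something much stronger: because the planned model is negative binomial, 0.82 is its alpha and the true power is about 30%. The article does not support that. An alpha of 0.82 cannot produce the printed 81%, whereas a linear variance comes close to both printed figures under a single smaller comparison. Negative binomial regression also exists in a constant-dispersion form, and Statistical analysis does not say which form is meant. The 30% is therefore a conditional case.

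A reader might also infer that the change of effect was meant to conceal the cost of overdispersion. Both effects are printed, and the text says openly that overdispersion lowers power. What is missing is a like-for-like figure.

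Finally, a condensed article may leave the site-weeks and the variance function to the full protocol. That is fair for the omission taken alone. The finding here is that printed results disagree with printed inputs.

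**Conclusion.** The point holds in this form: neither 86.7% nor 81% is the power of 14 sites with 4 baseline and 8 rapid weeks. The stated design gives 94 to 95% for the Poisson case, and 89 to 91% for 12.5 to 10 if variance is 1.82 × mean. The printed pair approximately fits 56 against 56 site-weeks, or 10 sites at 4 against 8 weeks, so on the better-supported reading it is conservative. For 12 to 10 with the same overdispersion, the stated design has about 74 to 77%. Non-reproduction is certain within the variants tried; the meaning of 0.82 is inferred.

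These figures rest on independent site-weeks and an unadjusted comparison. They make no allowance for serial correlation within site, or for the planned adjustment for calendar time, inpatient prevalence and staff vaccination.

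**What to change.** 1. Recalculate and restate both powers on 56 against 112 site-weeks. If a smaller comparison was intended, state it and justify it.
2. Give Poisson and overdispersed power for the same effect size. Reporting both 12 to 10 and 12.5 to 10 under each variance assumption would be clearest.
3. State the variance function to which 0.82 belongs. If it is variance = 1.82 × mean, say so. If it is the mean-dispersion alpha of the planned model, replace the 81% by about 28 to 30%.

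The cost is one recalculation and about two sentences, with no change to conduct. The analysis needs no change on this account, since the adjusted incidence rate ratio is already to be reported with its 95% CI.
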